Front-line users (clinicians, nurses) download the Vula mobile app onto their personal smartphones. The app is free of charge to download and is available on Android and iOS devices. Front-line users open the app, enter the patient data into text fields and upload de-identified images of the patient’s burn into the app. They can then send the referral along with a clinical question. The burn specialist on call is informed via instant messaging that a case has been uploaded and can then review the visually transmitted information and images and provide diagnostic and treatment advice. Referrals are transmitted to the burn care consultant or duty senior registrar at either Tygerberg Hospital or Red Cross Children’s Hospital in Cape Town. One of these individuals is on-site and able to receive referrals 24 hours a day. They are able to respond to referrals using a smartphone, PC or tablet. All of the information the front-line user entered is visible to the burns specialist, and they are able to interact with the front-line user via an SMS function within the app in real time. The app includes a server application that can store user information and de-identified patient data via the secure Vula cloud server.

Training programmes are offered to all facilities that use the app. Training sessions are 30 minutes long and focus on basic use of the application along with a test case. Staff training for using the system will be designed taking into consideration users’ different levels of experience with smartphones. Anxiety about using these kinds of devices is an issue that must be considered and the training should be designed to empower the staff and not intimidate. Continuous quality management is offered by the Vula Mobile team as well as by members of the research team. Technical problems are handled by the Vula support staff, while any issues with the study protocol or the referral process are handled by the research team. The app is routinely updated by the Vula Mobile team.

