The primary outcome measure in the evaluation plan is defined as adequate referrals. A burns specialist with vast experience of burn care will define appropriate referral. The specialist will go through all patient files and decide whether or not each case should have been referred to a dedicated burns unit or not. The ratio of LOS over %TBSA will be included as the secondary outcome.

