#### Data collection and data analysis to assess health impact

The data are retrospectively extracted by a research assistant from medical records at each hospital’s emergency department, including notes from the doctors, nurses and emergency medical services (EMS). Inclusion criteria will be burn injuries severe enough to remain at the hospital for at least one night or those being transferred to another health care facility. A standardized case report form based on World Health Organization (WHO) guidelines [25] will be used for the data collection on-site. Data will cover aspects relative to the injured patient (age, sex), the injury itself, some specific injury circumstances and information regarding referral. The data will be systematically collected on all injury cases to include TBSA, burn depth, Abbreviated Injury Scale (AIS), sex, mechanism of the burn and if the patient was transferred or treated and discharged.

Data will also be stored on the Vula Mobile cloud server. On any patient where the Vula app is used, their de-identified data, including all of the information mentioned earlier, will be stored in a secure password-protected cloud sever. Only the research team and a Vula administrator will have access to these data. Patients where the app is used will also need the data from their physical folders, as mentioned earlier, recorded as well.

The exposure of interest is use of diagnostic mHealth support. Patients with burn injuries where the doctor at point of care has used the app to receive diagnostic support from a burns expert will be considered as exposed. Patients with burn injuries where the app has not been used will be considered as non-exposed. Adequate referral assessed by a burns expert will be defined as the primary outcome. LOS per %TBSA will be considered as the secondary outcome.

A minimum sample size, based on the assumptions of a baseline rate of adequate referrals of 30% and about 50% exposure to the app, of 625 patients is required to show a difference of 10% referral rates between groups with 80% power (two-sided alpha = 0.05).

Logistic regression models will be used to investigate the effects of mHealth diagnostic support.

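### The primary outcome is one burns specialist's judgement from patient files, with no stated masking to app use, app advice or disposition, so it is not protected from knowledge of exposure

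*Protocol article*

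**What the plan says.** Under the heading on acute health outcome measures, the article says: "The primary outcome measure in the evaluation plan is defined as adequate referrals". It then fixes who decides and from what: "A burns specialist with vast experience of burn care will define appropriate referral", and "The specialist will go through all patient files and decide whether or not each case should have been referred to a dedicated burns unit". The data collection section repeats the point: "Adequate referral assessed by a burns expert will be defined as the primary outcome".

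The same section describes the source material. A research assistant extracts data from emergency department records, which include doctors', nurses' and ambulance notes, onto a standardized case report form. The extracted items include "some specific injury circumstances and information regarding referral" and "if the patient was transferred or treated and discharged". Patients on whom the app was used also have a record on the app's cloud server, to which the research team has access.

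A patient counts as exposed when the treating doctor used the app to get support from a burns expert. The system description says what that expert does: "review the visually transmitted information and images and provide diagnostic and treatment advice". These experts are the on-call burn specialists at two tertiary hospitals.

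No section masks the rating specialist to app use, app advice or disposition. None says whether the specialist may rate a case on which they gave advice.

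**The concern.** The outcome is a yes/no clinical opinion with no written criteria in the article, so knowledge of what happened can sway it. Two kinds of knowledge matter.

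- **App advice.** The exposure is a burns expert's view of the patient, and the outcome is a burns specialist's view of whether the patient should have been referred. A rater who knows what a colleague advised, or who gave the advice, may tend to agree with it.
- **Disposition.** A rater who knows whether the patient was transferred may judge need in the light of that.

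If either pull is stronger in one group, the groups differ on the primary outcome for reasons unrelated to quality of care. The planned logistic regression can adjust for patient characteristics. It cannot undo an outcome that was classified differently by exposure.

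**Working it through.** **1. The plan's own setting.** The data collection section gives a 30% baseline, about 50% exposed, a 10-point difference, 80% power, two-sided alpha 0.05 and 625 patients. With the pooled two-proportion formula, 30% against 20% needs 294 per group, or 313 with continuity correction. That is 626 in total and matches 625 to within rounding. A rise from 30% to 40% would need 712 without correction. The direction of the planned difference is a separate matter. Here 625 only supplies the group size, 625 / 2 = about 312.

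**2. Which way the pull acts.** The article asks for a judgement of need and collects disposition. Assume a referral is adequate when the two agree. If the rater sides with the app advice:

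| Was the advice followed? | Judged need | Disposition | Rating |
|---|---|---|---|
| Yes | same as advice | same as advice | adequate |
| No | same as advice | opposite | inadequate |

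The pull therefore favours the app only to the extent that advice was followed. The article gives no figure for this.

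**3. A pull common to both groups.** Suppose knowing the disposition turns a share q of inadequate cases into adequate ones in each group. A rate p becomes p + (1 − p)q, and a difference D becomes (1 − q)D. This creates no difference where there is none, but it shrinks a real one. A false effect needs a pull that differs by exposure.

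**4. Illustration of a differential pull.** Assume no true effect, 30% adequate among the unexposed, 30% + d among the exposed after the shift, and n = 312 per group. The values of d are assumptions.

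- Standard error under the null: se0 = √(2·m(1 − m)/n), where m is the mean of the two rates.
- Standard error under the shift: se1 = √((p0(1 − p0) + p1(1 − p1))/n).
- Rejection probability = Φ((d − 1.96·se0)/se1) + Φ((−d − 1.96·se0)/se1).

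| d | Exposed ratings moved (of 312) | Share of the 70% inadequate | se0 | se1 | Two-sided rejection |
|---|---|---|---|---|---|
| 0.02 | about 6 | 0.02/0.70 = 2.9% | 0.0370 | 0.0370 | 8.4% |
| 0.05 | about 16 | 0.05/0.70 = 7.1% | 0.0375 | 0.0375 | 26.6% |
| 0.08 | about 25 | 0.08/0.70 = 11.4% | 0.0379 | 0.0378 | 56.0% |

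With d = 0.02, the 8.4% is 7.8% in favour of the app plus 0.6% against it. Relabelling about 14% of the inadequate exposed cases (0.10/0.70) would produce the whole 10-point target difference, with about 75% rejection.

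**The case against.** The strongest reply is that the mechanism is inferred.

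- **File content.** Reading that the specialist goes through every patient's file, one might infer that the files show app use and the expert's advice. The article does not say so. App data sit on a separate server, advice is exchanged inside the app, and the article does not say whether the rater sees the raw folder, the case report form or the app record. This stands: the outcome is unprotected from knowledge of exposure, but it is not shown to depend on it.
- **One-sidedness.** One might infer that only exposed files reveal specialist input. Disposition is collected for all cases. The article treats telephone referral as the ordinary route and warns that clinicians not using the app may have sought help through other social media. This also stands: the contrast between groups may be weaker than it first looks.
- **Direction.** A bias in favour of the app assumes the advice was mostly followed. This stands, as step 2 shows.
- **Condensed article.** Masking could be set out in a full protocol that is not shown. This stands in part. The point does not rest on silence alone, because the article fixes a concrete procedure of file review by one specialist. Its discussion of methodological challenges covers contamination of controls and choice of outcome, but not this.

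**Conclusion.** The procedure as written leaves a subjective primary outcome open to rating that differs by exposure, and regression adjustment would not remove such a difference. The most plausible direction is in favour of the app, provided that its advice was usually followed.

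The size is unknown. The rejection rates of about 8%, 27% and 56% show how sensitive the comparison is to assumed shifts of 2, 5 and 8 points. They do not estimate the bias. They also rest on a 30% baseline, about 312 patients per group, an unadjusted comparison and no true effect.

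A reader might go further and conclude that the rating is known to depend on exposure, or that the result is bound to favour the app. The article supports neither. This should be fixed, but it does not by itself invalidate the design.

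**What to change.** 1. From the standardized case report form, the research assistant prepares a presentation summary in the same way for every patient (for example age, TBSA, burn depth, mechanism and AIS). App use, app images, expert advice, disposition and LOS are left out. Comorbidity belongs in the summary only if it is recorded for both groups. The ethics section mentions it for patients without the app, so its presence could itself reveal exposure.
2. From that summary alone, the specialist records whether the patient needed a burns unit, yes or no.
3. A program derives adequacy by comparing that judgement with the recorded disposition. The judgement of need and the transfer item are already in the plan. What is new is the masking, the explicit derivation and step 4.
4. The assessor does not rate a case on which they gave advice. Such cases go to another specialist.

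The rating is described as still to come and uses retrospective records, so the change can be made before it begins. The cost is abstraction time and less detail than the full file. No second reading of each case is needed, although step 4 may call for another specialist for a few cases. Some dependence may remain if the TBSA or depth recorded for exposed patients already reflects the expert's input, and the report should say so.

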#### Data collection and data analysis to assess health impact

The data are retrospectively extracted by a research assistant from medical records at each hospital’s emergency department, including notes from the doctors, nurses and emergency medical services (EMS). Inclusion criteria will be burn injuries severe enough to remain at the hospital for at least one night or those being transferred to another health care facility. A standardized case report form based on World Health Organization (WHO) guidelines [25] will be used for the data collection on-site. Data will cover aspects relative to the injured patient (age, sex), the injury itself, some specific injury circumstances and information regarding referral. The data will be systematically collected on all injury cases to include TBSA, burn depth, Abbreviated Injury Scale (AIS), sex, mechanism of the burn and if the patient was transferred or treated and discharged.

Data will also be stored on the Vula Mobile cloud server. On any patient where the Vula app is used, their de-identified data, including all of the information mentioned earlier, will be stored in a secure password-protected cloud sever. Only the research team and a Vula administrator will have access to these data. Patients where the app is used will also need the data from their physical folders, as mentioned earlier, recorded as well.

The exposure of interest is use of diagnostic mHealth support. Patients with burn injuries where the doctor at point of care has used the app to receive diagnostic support from a burns expert will be considered as exposed. Patients with burn injuries where the app has not been used will be considered as non-exposed. Adequate referral assessed by a burns expert will be defined as the primary outcome. LOS per %TBSA will be considered as the secondary outcome.

A minimum sample size, based on the assumptions of a baseline rate of adequate referrals of 30% and about 50% exposure to the app, of 625 patients is required to show a difference of 10% referral rates between groups with 80% power (two-sided alpha = 0.05).

Logistic regression models will be used to investigate the effects of mHealth diagnostic support.

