### User perspective

One aspect of evaluation, often overlooked, is how the teleconsultation system is experienced by the users (front-line users and burns experts). Usability evaluation includes both perceived ease of use and perceived usefulness and can help with identifying whether the user encounters problems while using the system. Ongoing usability evaluations within the project have a mixed-methods approach. Semi-structured interviews have been conducted to capture the burns experts’ views on the consultation system. The experts were encouraging about the system and willing to adopt it. They agreed that the app could contribute to increased education opportunities and better ability to advise and diagnose [16].

Both front-line health care providers and burns experts has been invited to ‘think-aloud sessions’ where they express their thoughts, feelings and opinions while using the app. Furthermore, a structured questionnaire (Health-Information Technology Usability Scale [17]) will be disseminated when the app has been used more frequently.

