### Health impact

The ultimate goal of the system is to improve health outcomes of the patients. In the first step, we have focused on the short-term clinical impact of the system, but when the system has been used for a longer period of time it will obviously be interesting to also study the potential long-term impact of the system.

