Despite these challenges and the few extra minutes it takes to use the app for clinical consultation, the system is expected to improve care delivery and facilitate local management whenever possible, which reduces stress of transport and long distances to travel for patients and caregivers. Additionally, care is likely to be enhanced through the timely addition of specialist advice and knowledge through the system.

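### The stated 625 patients do not give 80% power for a rise in adequate referrals from 30% to 40%; that needs 712 (752 with continuity correction), and 625 gives about 75%

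*Protocol article*

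**What the plan says.** The only sample-size statement is in the protocol article, under Data collection and data analysis to assess health impact. Its assumptions are a "baseline rate of adequate referrals of 30% and about 50% exposure to the app". From these it concludes that a minimum "of 625 patients is required to show a difference of 10% referral rates between groups with 80% power (two-sided alpha = 0.05"). No value for the exposed group is given, so the reader cannot tell from this sentence whether a rise or a fall is meant.

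The same section fixes the endpoint: "Adequate referral assessed by a burns expert will be defined as the primary outcome". Two other places indicate the expected direction. Under Health impact: "The ultimate goal of the system is to improve health outcomes of the patients". Under Other methodological and ethical considerations: "the system is expected to improve care delivery and facilitate local management whenever possible".

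**The concern.** A high rate of adequate referral is good, and the system is meant to help. The natural alternative is therefore a rise from 30% to 40%. A binary outcome has more variance at 40% than at 20%, so from a 30% baseline a 10-point rise needs more patients than a 10-point fall. The figure 625 looked too small for the rise.

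At stake is how the primary result will be read. With exactly 625 patients, the chance of missing a true 10-point gain would be about 25%, not the 20% implied. A null result would be judged against power that the study did not have.

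**Working it through.** **Inputs, all from the sample-size sentence.** Baseline p1 = 0.30; absolute difference d = 0.10; half exposed, so two equal groups; two-sided alpha 0.05 (z = 1.960); power 80% (z = 0.8416); stated total 625, or 312.5 per group. The direction is not an input there. It is inferred from the two statements of purpose and expectation.

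**Formulas.** With m = (p1 + p2)/2, the pooled-variance size per group is

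n = [1.960 × √(2m(1 − m)) + 0.8416 × √(p1(1 − p1) + p2(1 − p2))]² / d²

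and the continuity-corrected size is

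n_c = (n/4) × [1 + √(1 + 4/(n·d))]².

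**Step 1: reproduce 625, using 30% against 20%.** Here m = 0.25.
- n = [1.960 × √0.375 + 0.8416 × √0.37]² / 0.01 = (1.2002 + 0.5119)² / 0.01 = 293.15 per group, 586.3 in total (294 per group after rounding up, 588).
- n_c = 73.29 × (1 + √1.1364)² = 312.8 per group, 625.7 in total (313 per group after rounding up, 626).

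This matches the stated figure to rounding. The mirror case, 70% against 80%, has the same variances and gives the same result.

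**Step 2: the expected improvement, 30% against 40%.** Here m = 0.35.
- n = [1.960 × √0.455 + 0.8416 × √0.45]² / 0.01 = (1.3221 + 0.5646)² / 0.01 = 355.9 per group. Rounded up, this is 356 per group, **712** in total.
- n_c = 88.99 × (1 + √1.1124)² = 375.7 per group. Rounded up, this is 376 per group, **752** in total.

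The shortfall of 625 is 712 − 625 = 87 patients (87/712 = 12%). With the correction kept, it is 752 − 625 = 127.

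**Step 3: power of 625 for 30% against 40%.**
- Uncorrected: (0.10 − 1.960 × √(0.455/312.5)) / √(0.45/312.5) = (0.10 − 0.0748)/0.0379 = 0.664, which is **74.7%** power.
- Corrected: subtracting a further 1/312.5 = 0.0032 from the numerator gives 0.580, which is **71.9%**.
- The rise detectable with 80% power at 625, uncorrected, is from 30% to about 40.7%, or 10.7 points.
- For comparison, 625 patients have 82.5% power (80.0% corrected) for a fall from 30% to 20%.

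**Step 4: can another method yield 625 for 30% against 40%?**

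| Variant, 30% vs 40% | Total |
|---|---|
| Unpooled variance | 708 |
| Arcsine | 712 |
| Logistic regression, binary covariate | 712 |
| Wald test on log odds ratio | 718 |
| Allocation ratios 0.8 to 1.5 | 714 to 748 |
| One-sided, uncorrected / corrected | 562 / 600 |

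None gives 625. Reading 30% as the overall rate (25% against 35%) gives 658, or 698 corrected, and does not match either.

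**The case against.** **Only a difference is claimed, and the test is two-sided.** It is true that the sentence never mentions 40%, and that 625 has its stated power for a 10-point fall. But a two-sided test does not make the two directions equally costly. From 30%, the fall needs 626 (corrected) and the rise 752 (corrected). A claim about an undirected 10-point difference has to cover the larger figure, and 625 does not.

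**The number may be right and the label wrong.** This stands as a possibility. If 30% was meant as the rate of inadequate referrals, to be reduced to 20%, then 625 fits an improvement and the baseline wording is what needs correcting. A reader might infer that the calculation was simply run in the wrong direction. The documents do not support that as a fact, because both explanations give the same number.

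**625 is a minimum in a records cohort.** This also stands. Data come from medical records over a set window (January 2017 to February 2018), and the number of eligible records is not given. A reader might conclude that the study itself is underpowered. Only the quoted minimum is shown to be short; the achieved size may be larger or smaller.

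**Exposure may be below half.** A reader might infer this from the User perspective section, where a usability questionnaire "will be disseminated when the app has been used more frequently". That remark gives no proportion of study patients exposed, and elsewhere the app is described as part of standard care. It is no basis for challenging the 50% assumption.

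**Conclusion.** The sentence cannot stand as written for the improvement that the article expects. If adequate referrals are to rise from 30% to 40%, the minimum falls short by 87 patients (127 with continuity correction) and the power is about 5 points below the stated 80% (about 8 points with the correction).

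This rests on the article's own inputs, equal groups, an unadjusted comparison and the inferred direction. The size is modest: the detectable rise is 10.7 points instead of 10, and neither the endpoint nor the planned analysis is affected. It still matters because this is the only sample-size statement and it concerns the primary outcome. Whether the number or the baseline label is at fault is for the authors to say.

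**What to change.** First state the direction of the 10-point difference and whether the 30% is the rate of adequate or inadequate referrals. Then:

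- **If adequate referrals are to rise from 30% to 40%:** either keep 625 as the minimum and restate the power as about 75% (72% with continuity correction), or the detectable rise as about 10.7 points (uncorrected); or give the required size as 712 (752 with continuity correction). Name the method. The stated 625 matches only a continuity-corrected calculation, so 752 is the like-for-like figure, and giving 712 means a change of method that should be declared.
- **If 30% is the inadequate rate:** correct the baseline to 70% adequate, rising to 80%, keep 625 and say that it includes a continuity correction.

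Restating the power or the label changes wording only. The cost is a slightly less favourable stated figure in the first case. If the required size is raised instead, whether it can be met depends on how many eligible records the window holds, which the article does not report.
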